**Table 3 TAB3:** Eligibility criteria SIP: symptomatic irreversible pulpitis; VAS: visual analog scale

Inclusion criteria	Exclusion criteria
Participants with a tooth	Participants with pacemakers or implantable cardioverter-defibrillators
diagnosed with SIP requiring pulpectomy	
Permanent teeth	
Teeth with spontaneous pain	
Teeth with a positive response to an electric pulp test	
Participants aged ≥18 years	
Participants who can complete the VAS assessment independently	
Teeth without periapical lesions	
Periodontal pocket depth of the target tooth <4 mm	
Absence of furcation lesions in the target tooth	
Alveolar bone resorption of the target tooth	
< one-third of the root length	
Participants who provide written informed consent	

Intervention

After enrollment, the following procedure will be performed by operators. Following infiltration anesthesia, the targeted tooth will be isolated with a dental dam, and an access cavity will be prepared in the SIP tooth's pulp chamber using a rotary cutting instrument. Only minimal pulp exposure will be created to allow insertion of the electrode tip. The tip electrode of Root ZX3 was then inserted into the pulp tissue, and HFC (Mode 4; 530 kHz) was applied three times. The access cavity will be sealed with a temporary restorative material (Caviton; GC Dental Industrial Corporation, Tokyo, Japan). Finally, a questionnaire assessing post-treatment pain will be provided to the patient.

If the target tooth presents with extensive caries and severe structural loss, it will be temporarily built up with composite resin to facilitate isolation and treatment; thereafter, the above intervention will be carried out. Any other usage of high-frequency electrosurgery instruments during treatment with Root ZX3 will be prohibited.

At 2 ± 1 weeks after the intervention, the pain questionnaires will be collected, and horizontal and vertical percussion was evaluated by operators. Then, pulpectomy was performed without infiltration anesthesia to assess pain during treatment. After the study, procedures are completed, participants were followed up as part of routine care, and appropriate treatment was provided as needed.

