All intervention procedures will be documented in the electronic medical record by the operators to enhance protocol adherence. Criteria for halting the intervention include a participant’s request to withdraw or modify their assigned treatment, any clinical deterioration or onset of comorbid conditions, and any situation where the research team deems continued participation unsuitable.

Primary endpoint

The primary endpoint is the relief of spontaneous pain on postoperative day 0. The primary outcome will be expressed as the proportion of participants in whom spontaneous pain has completely resolved on postoperative day 0.

Secondary endpoints

The secondary endpoints are: (1) Relief of spontaneous pain on postoperative days 1, 2, 3, and 7; (2) Improvement in occlusal pain on postoperative days 0, 1, 2, 3, and 7; (3) Pain during pulpectomy was experienced two weeks after the intervention; (4) Improvement in percussion pain two weeks after intervention.

Safety endpoints

For devices in this category, the following adverse events require particular attention: burns, convulsions, muscle contractions, tissue and mucosal injury and inflammation, hematoma, electric shock, cardiac arrest, and perforation. To date, such adverse events have not been reported with Root ZX3. All adverse events will be recorded and assessed for severity and causality.

Data collection

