Statistical design

The proportion of participants in whom spontaneous pain is resolved on postoperative days 0, 1, 2, 3, and 7 will be calculated using all enrolled cases as the denominator and the number of participants whose spontaneous pain has resolved as the numerator. The mean, standard deviation, median, minimum, maximum, and quartiles of preoperative and postoperative occlusal pain (VAS values) were calculated on days 0, 1, 2, 3, and 7, and those of percussion-induced pain (VAS values) will be calculated at 2 ± 1 weeks postoperatively. Fisher's exact test will analyze the presence or absence of occlusal pain (based on VAS values) on postoperative days 0, 1, 2, 3, and 7, as well as the presence or absence of improvement in percussion-induced pain (based on VAS values) at 2 ± 1 weeks postoperatively, compared with baseline. The proportion of participants with pain at 2 ± 1 weeks postoperatively will be calculated by using all cases as the denominator and the number of participants with pain as the numerator.

Participants who discontinue participation in the study will be excluded from the efficacy analysis. Data with missing values are not discarded and are subject to statistical analysis.

Access to data

The final dataset generated by this study will be accessible exclusively to the PI. Direct access for other research personnel is not permitted under this protocol.

Monitoring

A designated research staff member will conduct monitoring based on standard operating procedures, delivering findings to the PI within 14 days of the evaluation. Should any adverse events or unforeseen complications arise, the PI will provide medical intervention, notify the CRB, and brief the study team. Given that Root ZX3 has already received approval from the Pharmaceuticals and Medical Devices Agency, a separate data monitoring committee is not required.

Potential benefits and harms

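### Spontaneous-pain resolution is to be calculated over everyone enrolled, yet participants who discontinue are excluded from the efficacy analysis; the two rules conflict, including for the primary endpoint

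*Protocol article*

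**What the plan says.** All of the relevant text is in the protocol article, under Materials and methods.

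- **Primary endpoint:** "The primary outcome will be expressed as the proportion of participants in whom spontaneous pain has completely resolved on postoperative day 0".
- **Secondary endpoints:** the first is "Relief of spontaneous pain on postoperative days 1, 2, 3, and 7".
- **Statistical design, first paragraph:** the proportions for days 0, 1, 2, 3 and 7 are calculated "using all enrolled cases as the denominator and the number of participants whose spontaneous pain has resolved as the numerator". For pain at two weeks the wording is similar: "using all cases as the denominator and the number of participants with pain as the numerator".
- **Statistical design, second paragraph:** "Participants who discontinue participation in the study will be excluded from the efficacy analysis". The next sentence adds: "Data with missing values are not discarded and are subject to statistical analysis".
- **Intervention, halting criteria:** these include a participant asking to leave or to change treatment, clinical worsening, and "any situation where the research team deems continued participation unsuitable".
- **Intervention, two-week visit:** the questionnaires are collected at 2 ± 1 weeks. "Then, pulpectomy was performed without infiltration anesthesia to assess pain during treatment".

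The SPIRIT checklist in the appendix (items 27b and 27c) points to the article itself for who is analysed and how missing data are handled.

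**The concern.** The two denominator rules agree only if nobody discontinues. After one discontinuation, the first gives a denominator of 10 and the second a denominator of 9. Day 0 is named in the first rule and is part of the efficacy analysis covered by the second, so the primary endpoint is affected as well as the later days.

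The exclusion is also a poor rule in itself. In an open-label, single-arm trial, a participant whose pain persists has an obvious reason to withdraw or to ask for other treatment, and clinical worsening is a listed reason to halt. Removing such a person from the analysis removes a treatment failure because it was a failure. The rule could also be chosen with the outcomes already known.

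The estimates are the main product of the trial. The Sample size section says that the 10 cases will be used to plan later randomized trials.

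**Working it through.** **Plan's own figure.** There is none to reproduce. The sample size is a feasibility choice, with no power, target rate or success threshold.

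**Inputs**
- N = 10 enrolled (Sample size section).
- s = number resolved on a given day when everyone enrolled is counted. The documents give no value; s = 7 is assumed for illustration and the full range is shown below.
- Number who discontinue: not given; one is assumed, then two.

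**Formulas for one discontinuation**
- All-enrolled rule: s/10.
- Exclusion rule, participant unresolved that day: s/9. Change = s/9 - s/10 = s/90.
- Exclusion rule, participant resolved that day: (s - 1)/9. Change = (s - 1)/9 - s/10 = (s - 10)/90.

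**Results for s = 7, with exact (Clopper-Pearson) 95% intervals**

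| Rule | Proportion | 95% CI | Change |
|---|---|---|---|
| All enrolled | 7/10 = 70.0% | 34.8 to 93.3 | reference |
| One unresolved participant dropped | 7/9 = 77.8% | 40.0 to 97.2 | +7.8 points |
| One resolved participant dropped | 6/9 = 66.7% | 29.9 to 92.5 | -3.3 points |

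**Range over s.** Dropping one unresolved participant adds at most 9/90 = 10.0 points (s = 9). Dropping one resolved participant subtracts at most 9/90 = 10.0 points (s = 1).

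**Two unresolved participants dropped, s = 7.** 7/8 = 87.5%, which is +17.5 points.

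**Direction by day.** The exclusion removes all of a participant's efficacy ratings, including those made before leaving. Someone pain-free on days 1 and 2 who leaves on day 5 because pain returned would lower the day 1 and 2 proportions if dropped (70.0% to 66.7% with s = 7). On days when that person was in pain, or had no rating and so could not enter the numerator, dropping raises the proportion (70.0% to 77.8%).

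**Secondary matter: unscheduled endodontic treatment of the study tooth.** The numerator does not depend on what resolved the pain. Assume one participant is re-treated for pain before a later rating, remains in the study and is then pain-free, and 7 of the other 9 are resolved. As written the result is 8/10 = 80%; with that participant counted as not resolved it is 7/10 = 70%. A re-treated participant who is still in pain already counts as not resolved. Ratings made before the re-treatment do not change.

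**The case against.** **The article is condensed, and the full protocol and any SAP are not shown.** This would answer a complaint that a rule is missing. Here both rules are stated and they disagree. One could reconcile them by reading the exclusion as a qualification of the first rule, but the denominator would then not be everyone enrolled, and exclusion related to outcome would remain. The sentence on missing values does not settle which rule prevails.

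**The practical importance is limited.** This stands in part. The spontaneous-pain analysis is descriptive, in 10 participants, with no threshold and no test, and the intervals above overlap almost entirely. The primary rating is made typically 4 to 6 hours after the procedure, which leaves little time for anyone to leave before it. The exclusion nevertheless removes day 0 for someone who leaves later.

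**A reader might infer that the exclusion always raises the day 1 to 7 proportions.** The documents do not support that. As the day-by-day check shows, it also removes favourable earlier ratings.

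**A reader might also infer that the plan will credit the device with relief produced by early re-treatment.** The article never mentions early re-treatment of the study tooth, and it does not equate halting the intervention with discontinuing participation. Re-treatment for pain fits the halting criteria, so such a participant might well be taken off study and not scored as resolved. How to score treatment after an unscheduled procedure is mainly a rule not written here, and it affects only secondary ratings made after that procedure. It therefore supports an optional addition, not the main point.

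**Conclusion.** The contradiction is real and sits in adjacent paragraphs of one section. It affects the primary day-0 proportion and the secondary proportions on days 1, 2, 3 and 7. With one discontinuation among 10, the figure moves by +7.8 or -3.3 points when 7 are resolved, and by between -10 and +10 points over all possible counts. The direction on a given day depends on the participant's status that day. For someone who leaves because of persistent pain, dropping raises the proportion on the days of pain.

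The size rests on assumed numbers of discontinuations and of resolved participants; if nobody discontinues there is no difference. The point concerns the reported estimate, not a test decision, because no test is planned for spontaneous pain. It should be corrected before analysis. The article reports recruitment until December 2027 and no interim analysis, so there is time.

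**What to change.** For the binary spontaneous-pain endpoints:

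1. Delete the sentence excluding those who discontinue, and keep everyone enrolled as the denominator, as already stated. No new analysis set is needed.
2. Use ratings made before discontinuation as observed. Count ratings missing after discontinuation as not resolved.
3. Report the number of discontinuations with reasons, and give an observed-cases proportion for each day beside the main figure.
4. As a secondary addition, count spontaneous pain as not resolved at ratings made after unscheduled endodontic treatment of the study tooth for pain, and report how many such treatments occurred. The reason is that the Potential benefits and harms section frames the aim as showing that the device is effective on its own. A day-0 rating made before such treatment stands as observed.

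The change is limited to spontaneous pain on purpose. The occlusal analysis concerns presence or absence of pain and goes into Fisher's exact test, so a not-resolved score does not carry over directly. For pain during the two-week pulpectomy the numerator is participants with pain, so keeping unassessed participants in the denominator would favour the device (for example 2/10 = 20.0% against 2/9 = 22.2%).

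The cost is a few sentences in the analysis text and, for item 4, one case report form entry for the date and type of unscheduled treatment, taken from the electronic medical record. Because the questionnaires are collected at the two-week visit, anyone leaving earlier should be asked to return theirs so that the day-0 rating is not lost. Care and sample size do not change. The downside is that the proportions may look slightly less favourable and participants who leave for unrelated reasons count as not resolved; the observed-cases figure lets the reader see how much that matters.

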## Materials and methods

Trial design

This is a single-center, open-label, single-arm clinical trial. The PICO (Population, Intervention, Comparison, and Outcome) framework for this study is summarized in Table 1. To ensure comprehensive reporting, this protocol adheres to the Standard Protocol Items: Recommendations for Interventional Trials (SPIRIT) criteria [8]. We have included the finalized SPIRIT checklist in the Appendix.

**Table 1 TAB1:** PICO question SIP: symptomatic irreversible pulpitis; HFC: high-frequency current

Criteria	Description
P (Participants)	Patients with a tooth diagnosed with SIP
I (Intervention)	Application of HFC
C (Control)	Not applicable (single-arm trial)
O (Outcome)	Proportion of spontaneous pain resolved after intervention

Participant timeline

The schedule of enrollment, interventions, and assessments is summarized in Table 2.

**Table 2 TAB2:** SPIRIT figure

Timepoint	Enrolment &	Assessment 1	Assessment 2
	intervention	(Day 1, 2, 3, or 7	(Two weeks after intervention
	(Day 0)	after intervention)	range ±7 days)
Enrolment			
Eligibility screening	X	―	―
Informed consent	X	―	―
Intervention			
Intervention	X	―	―
Clinical assessment			
Inspection	X	―	X
Pain during treatment	―	―	X
Percussion	X	―	X
Adverse events	X	―	X
Questionnaire survey	―	X	―

Study setting

All clinical trial activities will take place at Nagasaki University Hospital in Nagasaki, Japan.

Sample size

As the clinical application of Root ZX3 for SIP lacks systematic evaluation, no preliminary data are available for a formal power calculation. This study is therefore designed as an exploratory, single-arm feasibility trial to obtain initial estimates of safety, effect size, and clinical variability.

A total sample size of 10 participants was selected based on feasibility requirements for early-phase device investigations, in which small cohorts (typically 10-20) were appropriate for identifying procedural concerns before larger trials. Given the absence of prior effect-size estimates for immediate postoperative pain relief with this device, a formal calculation would lack a meaningful basis. Data from these 10 cases will provide the necessary preliminary estimates to determine the power and sample size for future multicenter randomized controlled trials.

Eligibility screening

Eligibility will be confirmed by operators in accordance with the criteria listed in Table 3.

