After the intervention, participants will be given a pain diary to record their pain levels and the dose and frequency of any analgesic medication taken. Spontaneous, occlusal, and percussion pain will be evaluated using a questionnaire. Postoperative Pain Assessment on postoperative day 0 was conducted after the effects of local anesthesia had completely worn off, typically 4 to 6 hours following the procedure. Occlusal and percussion pain will be assessed via a 100 mm visual analog scale (VAS; endpoints defined as 100 for unbearable pain and 0 for no pain), and participants will be instructed to indicate their pain level by marking the VAS line. Operators will assess pain during pulpectomy, which will be performed two weeks after the intervention. For percussion testing, clinical operators will conduct both vertical and horizontal percussion using the blunt end of a dental mirror handle to evaluate the status of the periodontal ligament and periapical tissues. To ensure force consistency and provide a baseline for the participant, the test is first applied to an adjacent or contralateral healthy tooth with a gentle, controlled tapping force. The participant’s response is then recorded using a VAS. These assessments are conducted at baseline (Day 0) and at the two-week follow-up visit.

Data management

Upon obtaining written informed consent, the operator will complete the identification and case registration forms. These documents are subsequently integrated into the electronic medical record and forwarded to the Principal Investigator (PI), who maintains them within the secure research file. To ensure participant confidentiality, a unique research identification number, consisting of a numeric code and a symbol, is assigned to each participant upon enrollment. This identifier is deliberately kept separate from any personal information, such as initials or medical record IDs, that could directly identify an individual.

All study-related documentation, including case report forms, will be managed exclusively using these identification numbers to maintain anonymity. While the PI utilizes these codes for general data handling, a master identification list, linking names and medical record IDs to their respective study codes, will be maintained separately. This list is stored in a secure, lockable cabinet for a minimum of five years post-study, ensuring that participant identification remains possible only when strictly necessary and authorized.

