Reducing treatment time may lessen the burden on both participants and operators. If this study demonstrates that Root ZX3 alone is effective in managing SIP, it may expand treatment options and potentially benefit a wide range of patients. Possible side effects of the intervention include: (i) burns; (ii) spasms and muscle contractions; (iii) tissue and mucous membrane damage and inflammation; (iv) tissue injury; (v) burns or injury to other parts of the body of the participants due to improper contact with the counter-rod; (vi) hematoma; (vii) hypersensitivity to electric stimulation; (viii) cardiac arrest; (ix) iatrogenic injury to surrounding tissues; and (x) perforation.

Potential device malfunctions include: (i) ignition or explosion of flammable substances or gases; (ii) unintended output; (iii) unintended power increase or configuration change; (iv) malfunction due to electromagnetic interference; (v) malfunction due to wire breakage; (vi) malfunction due to poor contact; (vii) high-frequency shunt or leakage; (viii) interference with other equipment due to electromagnetic wave; and (ix) malfunction of an implantable cardiac pacemaker or implantable defibrillator. All such risks will be explained to participants during the consent process.

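### The named percussion-pain outputs cannot separate worsened teeth from unchanged ones, although VAS readings are collected at both baseline and two weeks

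*Protocol article*

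**What the plan says.** All references are to the Protocol article, Materials and methods.

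- **Secondary endpoints.** Percussion enters as item "4) Improvement in percussion pain two weeks after intervention". The endpoint points in one direction only.
- **Data collection.** Vertical and horizontal percussion are done "to evaluate the status of the periodontal ligament and periapical tissues", and the response is recorded on a VAS. On timing: "These assessments are conducted at baseline (Day 0) and at the two-week follow-up visit".
- **Statistical design, summaries.** For occlusal pain the plan names "quartiles of preoperative and postoperative occlusal pain (VAS values) were calculated on days 0, 1, 2, 3, and 7". In the same sentence, for percussion, it names only "those of percussion-induced pain (VAS values) will be calculated at 2 ± 1 weeks postoperatively".
- **Statistical design, comparison.** The one named comparison of percussion pain with its starting value is the "presence or absence of improvement in percussion-induced pain (based on VAS values) at 2 ± 1 weeks postoperatively, compared with baseline".
- **Safety endpoints, and Potential benefits and harms.** All adverse events are recorded and assessed for severity and causality. The possible harms listed include "iatrogenic injury to surrounding tissues".
- **Table 2.** Inspection, percussion and adverse events are all scheduled on Day 0 and at the two-week visit.
- **Sample size.** "A total sample size of 10 participants was selected based on feasibility requirements for early-phase device investigations".

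**The concern.** A yes/no split on improvement puts two different outcomes into its second class: teeth that did not change and teeth that got worse. A tooth with no percussion pain at baseline cannot improve, so it gets the same code whether it stays pain-free or becomes painful. Such teeth are plausible, because Table 3 requires spontaneous pain and no periapical lesion but does not require percussion pain.

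The continuous summary does not fill the gap. With follow-up values only, a reader cannot say whether the average rose or fell.

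Two features make this worth correcting. Percussion is the one test the text itself links to the tissues around the root. The trial is also meant to supply first estimates of effect and clinical variability for later trials, and a change from baseline is the quantity such planning would use. Under Access to data, the final dataset is open to the principal investigator alone, so readers will depend on the summaries that are reported.

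**Working it through.** The plan gives no computed figure here. The 10 participants are a feasibility choice without alpha, power or effect size, so there is nothing to reproduce. The check asks whether data sets that differ in worsening can give identical named percussion outputs.

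**Inputs.** n = 10 (Sample size); VAS 0 to 100 mm at baseline and two weeks (Data collection); outputs as named under Statistical design. The individual values are constructed for illustration and do not come from the documents. One VAS value per participant and time point is assumed.

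**Data.** The two-week values are the same in every set: 0, 5, 10, 10, 15, 20, 30, 40, 50, 60. Only the baselines differ:

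- Set A: 30, 40, 45, 50, 60, 20, 30, 40, 50, 60
- Set B: 30, 40, 45, 50, 60, 0, 5, 10, 15, 20
- Set C: 5, 10, 15, 15, 20, 0, 5, 10, 15, 20

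**Formulas.** Change = two-week value minus baseline; improved if change < 0, unchanged if 0, worsened if > 0. Mean change = two-week mean minus baseline mean.

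**Results.**

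| Quantity | A | B | C |
|---|---|---|---|
| *Named in the plan* | | | |
| Two-week mean (SD), mm | 24.0 (20.2) | 24.0 (20.2) | 24.0 (20.2) |
| Two-week median; quartiles | 17.5; 10, 37.5 | 17.5; 10, 37.5 | 17.5; 10, 37.5 |
| Two-week minimum, maximum | 0, 60 | 0, 60 | 0, 60 |
| Improved | 5/10 | 5/10 | 5/10 |
| *Not named* | | | |
| Baseline mean, mm | 42.5 | 27.5 | 11.5 |
| Unchanged | 5/10 | 0/10 | 0/10 |
| Worsened | 0/10 | 5/10 | 5/10 |
| Largest rise, mm | 0 | 40 | 40 |
| Mean change, mm | −18.5 | −3.5 | +12.5 |

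Arithmetic for mean change:

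- A: the first five changes are −30, −35, −35, −40, −45 (sum −185) and the rest are 0, so −185/10 = −18.5.
- B: the same −185, plus rises of 20, 25, 30, 35, 40 (sum 150), so (−185 + 150)/10 = −3.5.
- C: five falls of 5 mm (sum −25), plus the same 150, so (−25 + 150)/10 = +12.5.

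The named outputs agree in all three sets, while the worsened count runs from 0 to 5 of 10 and the mean change takes either sign.

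**What a worsened count would add at n = 10.** Exact two-sided 95% intervals: 0/10 gives 0 to 30.8%; 1/10 gives 0.3 to 44.5%; 5/10 gives 18.7 to 81.3%. The chance of seeing at least one worsened participant is 1 − (1 − p)^10. For assumed true rates of 5%, 10%, 20% and 30% this is 40%, 65%, 89% and 97%. The count would be imprecise, but it would usually register a rate of 20% or more.

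**The case against.** The other side has real weight.

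- **Other safeguards exist.** A reader might infer that percussion is the trial's only scheduled sign of injury around the root. It is not. Table 2 schedules inspection and adverse events at the same visits, every adverse event is recorded and graded, and tissue injury, inflammation and perforation are singled out for attention. Occlusal pain is summarised before and after treatment, though only to day 7.
- **Worsening is not invisible.** A reader might infer that harm cannot appear in the results. A tooth that rose from 0 to 70 mm would push the reported two-week maximum to at least 70. The output would not show that the value was a rise. Both readings are held, so nothing is lost for good.
- **Identical outputs need a condition.** If five teeth rose by 40 mm instead of staying unchanged, from the same baselines, the two-week mean would differ by 5 × 40/10 = 20 mm and the planned summary would separate the cases. The outputs coincide only when the baselines differ in an offsetting way, as in the sets above. That condition cannot be checked from the outputs, because baseline is not among them.
- **This is an efficacy endpoint.** Percussion pain is listed under secondary endpoints, and the Introduction treats it as a symptom of the disease and a possible result of residual pulp. A rise in a single-arm trial is therefore not specific to the current. Treating every rise as a safety finding would be a preference, and the documents do not support it.
- **The article is condensed.** The phrase that carries the summary statistics over to percussion could be read as carrying over the preoperative values too, but the stated time point is two weeks only. A fuller document could add baseline or change tables. It would still inherit an endpoint and a comparison defined here as improvement or its absence.

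These arguments remove any claim of hidden harm and lower the severity. They do not remove the point that the stated classification merges two outcomes.

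**Conclusion.** The point holds in limited form. The percussion analysis named under Statistical design cannot distinguish worsened from unchanged teeth and cannot show the direction of the average change, although the readings for both are collected. Identical named outputs are compatible with anything from 0 to 5 worsened participants in 10 when 5 are scored as improved.

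This rests on three assumptions: that the percussion summary covers the follow-up visit only, as its stated time point says; that the comparison with baseline takes improvement yes/no as its input; and that no unseen document already adds baseline or change summaries. The data sets are illustrative; the documents give no rate of worsening.

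Severity is minor. The endpoint is secondary and descriptive in an exploratory 10-participant trial, and neither the primary endpoint nor data collection is affected.

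**What to change.** In Statistical design:

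1. Summarise percussion VAS at baseline, at 2 ± 1 weeks, and as the within-participant change, with the statistics already listed for occlusal pain.
2. Replace the two-way improvement classification with counts of improved, unchanged and worsened participants. Align the wording of the fourth secondary endpoint with this.
3. State that a marked rise is assessed for causality under the existing adverse-event rule in Safety endpoints, and is not presumed to be harm from the device.

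The cost is a change of analysis wording. No visit, measurement or participant is added. The possible downside is a less favourable table.

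### Fisher's exact test is prescribed for before-and-after comparisons in the same 10 participants, so the p-values for the occlusal and percussion pain endpoints are invalid, and testing only dichotomised VAS loses power

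*Protocol article*

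**What the plan says.** Under Trial design the article states: "This is a single-center, open-label, single-arm clinical trial". Table 1 gives the control as not applicable. Under Sample size: "A total sample size of 10 participants was selected based on feasibility requirements for early-phase device investigations".

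The Statistical design section names one inferential method, due to Fisher. For occlusal pain the wording is: "exact test will analyze the presence or absence of occlusal pain (based on VAS values". This applies at five time points, namely days 0, 1, 2, 3 and 7 after the procedure. For percussion pain the same method is to cover "the presence or absence of improvement in percussion-induced pain (based on VAS values) at 2 ± 1 weeks postoperatively, compared with baseline". These are five tests for secondary endpoint 2 and one for secondary endpoint 4. No paired test is named.

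Both outcomes are continuous. Under Data collection: "Occlusal and percussion pain will be assessed via a 100 mm visual analog scale". The full scale is used only descriptively: the mean, SD, median, range and quartiles "of preoperative and postoperative occlusal pain (VAS values) were calculated", and the same summaries are planned for percussion pain at two weeks. No VAS cut-off is given for presence of pain or for improvement.

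**The concern.** Fisher's exact test of two proportions assumes two independent groups. With one arm, the only thing to compare with baseline is the same participants later. A baseline-by-follow-up table of 10 against 10 counts 10 people as 20 and ignores who changed.

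The obvious alternative layouts do not help. If the test is applied to the paired cross-tabulation, it tests association between baseline and follow-up, not change. If everyone has pain at baseline, one row of that table is empty and p = 1 whatever happens afterwards.

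Percussion has a further problem. If the comparison with baseline is what is being tested, improvement is already a change and has no baseline value to enter in a table. If those words only define improvement, Fisher's test has no comparison group.

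At stake are the p-values for secondary endpoints 2 and 4, and the chance of detecting a real fall in VAS that stops short of the cut-off.

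**Working it through.** **Inputs.** From the article: n = 10, one arm, 100 mm VAS, Fisher's test on binary values against baseline. The article gives no alpha, p-value, effect size or cut-off, so there is no stated figure to reproduce. Assumed here: two-sided tests at 0.05.

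**1. Fisher against the paired test.**
Fisher, with x and y of 10 in pain: P(x) = C(10,x)·C(10,y)/C(20,x+y), summed over tables no more probable than the one observed. Exact McNemar, with b resolved and c new: twice the binomial(b+c, ½) upper tail at max(b,c).

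- 10 to 5, no new pain. Fisher: 2 × 252/15504 = 0.0325. McNemar: 2 × (½)^5 = 0.0625. The conclusion at 0.05 changes.
- 10 to 3, no new pain. Fisher: 2 × 120/77520 = 0.0031. McNemar: 2 × (½)^7 = 0.0156. Both fall below 0.05.
- 8 to 4, no new pain. Fisher: 2 × (9450 + 1200 + 45)/125970 = 0.170. McNemar: 2 × (½)^4 = 0.125. Here Fisher's p is the larger.
- 8 to 2. Fisher: 2 × (2025 + 100 + 1)/184756 = 0.023, always. McNemar depends on the resolved/new split: 6/0 gives 2/64 = 0.031, 7/1 gives 18/256 = 0.070, and 8/2 gives 112/1024 = 0.109. Fisher cannot tell these datasets apart.

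**2. Size under no change.** Exact enumeration of Fisher's rejection rate, by within-person correlation:

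| Pain prevalence | −0.3 | 0 | 0.3 | 0.6 |
|---|---|---|---|---|
| 0.5 | 0.029 | 0.013 | 0.003 | 0.0003 |
| 0.7 | 0.027 | 0.012 | 0.003 | 0.0003 |

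The rate depends on a correlation that the test ignores, but it stays below 0.05 in every scenario tried.

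**3. Cost of dichotomising.** If all 10 participants improve, none reaches 0 and presence means VAS > 0, Fisher gives p = 1.0. The exact signed-rank test gives 2/2^10 = 0.002.

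Simulated power, assuming baseline VAS 60 (SD 20), SD of the fall 25 mm and values bounded at 0 and 100. Ranges reflect separate simulation runs.

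| Mean fall | Fisher, >0 | >10 mm | >20 mm | >30 mm | Signed-rank on VAS |
|---|---|---|---|---|---|
| 30 mm | 2% | 9% | 24% | 35–37% | 90–92% |
| 40 mm | 9–10% | 29% | 52% | 62–63% | 99% |

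Exact McNemar at the >0 cut-off has 0.4% and 2.8% power, so changing only the binary test would not recover the loss.

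**The case against.** The strongest reply is about consequence. The primary endpoint is a plain proportion with no test. The trial calls itself exploratory, its purpose is preliminary estimates for later trials, and no decision or success criterion hangs on a p-value. All of this stands, and it limits the importance of the point.

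A reader might infer that Fisher's test will produce too many false positives. The calculations do not support that: the error runs both ways, and the size never exceeded 0.05 in the scenarios tried.

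A reader might also take the 2% power as a property of the plan. It is not. It needs presence to mean VAS > 0, which the article does not say, and a higher cut-off raises power considerably. Nor is the VAS thrown away, since it is summarised descriptively; the loss concerns the tests only.

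For percussion, the wording may only define improvement, which would make the fault one of unclear drafting. That is fair, but Fisher's test would then have nothing to compare.

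Finally, a separate analysis plan might name other methods. The article does not leave the choice open, however: it names a test, and that test does not suit the design.

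**Conclusion.** The point holds for secondary endpoints 2 and 4. An independent-groups test is prescribed for paired data, and none of the readings considered makes it a valid test of change from baseline. The p-values can be too small or too large, by enough to change a conclusion at 0.05 (0.033 against 0.0625). That rests only on n = 10 and the assumed two-sided 0.05 level.

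The power comparison (about 2% to 37% against about 90% for a 30 mm fall; about 9% to 62% against 99% for 40 mm) rests on an assumed VAS distribution and a range of cut-offs, so it shows the order of the loss rather than a prediction.

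This should be corrected before analysis, but it does not threaten the primary result.

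**What to change.** Amend the Statistical design section as follows.

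- Analyse within-participant VAS change with the exact Wilcoxon signed-rank test and a median change with 95% CI, for occlusal pain on each day and for percussion pain at two weeks. This is the essential part.
- If presence or absence of pain is kept, state the cut-off and use the exact McNemar test.
- Report percussion improvement as a proportion with an exact CI among participants with baseline VAS > 0. Table 3 does not require percussion pain at entry, and someone without it cannot improve.
- Label the six tests exploratory.

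The cost is a protocol amendment (version 1.2.0 is already recruiting) and one check on data. Statistical design refers to a preoperative occlusal VAS, but Table 2 shows no questionnaire at baseline, so the investigators must confirm that it is collected. Baseline percussion VAS is already covered under Data collection. No interim analysis is planned and recruitment is due to run to December 2027, so there is time to make the change before the data are analysed.
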